## 2. Methodology

### 2.1. Trial Design and Setting

A parallel-group, single-blinded, two-arm randomized controlled superiority trial compares the effectiveness of HRTP to TAU with a 1:1 allocation ratio. Quantitative and qualitative data will be used to examine the effect of HRTP on racial trauma, depression (primary outcomes), and functioning (secondary outcomes). The trial will take place in an urban city in the province of Ontario, Canada.

Conducting the study in Ottawa contributes to the generalizability of the findings due to the city’s demographic and cultural diversity. As Canada’s capital, Ottawa attracts individuals from across the country and around the globe, providing a considerable mix of racial, ethnic, and linguistic communities. Based on the 2021 Population Census, Black people represented the largest racialized group at 8.5%, while Arabs and South Asian people each represented 5.8% of the total population of the city (Statistics Canada, 2021). As of 2021, there are also some 46,500 Indigenous people living in the Ottawa area, making up 3.2% of the population (Statistics Canada, 2021). This diversity means that the study is more likely to capture a range of lived experiences, cultural contexts, immigration histories, and socioeconomic backgrounds, thereby strengthening the external validity of the findings. A broad and varied participant pool will help ensure results are applicable to other urban centres and potentially even to more rural or international settings that share similar multicultural characteristics.

This study will follow the ethical principles of the Canadian Code of Ethics for Psychologists (CPA, 2017) and the Ethical Conduct for Research Involving Humans (TCPS-2, 2014). Informed consent will be obtained from all participants. The pilot study has been approved by the Research Ethics Board (H-02-22-7613) of the University of Ottawa, ensuring the protection of participant privacy and confidentiality. Participants may withdraw from the study at any time without consequence.

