### 2.2. Sample Size, Randomization, and Allocation

A sample of 96 participants (48 per group) is needed for an 80% probability to identify a difference between the treatment and control group. The power analysis for the sample size estimation was based on the means, standard deviations, and clinical cut-off for the primary outcomes (RTS, TSDS; Williams et al., 2022c, 2023b). Drawing on previous research, we hypothesized a standard mean difference of between 0.36 and 0.52, between the treatment and control group, which translates to a 10–20% decrease in the primary outcomes (i.e., RTS, TSDS) for individuals at the endpoint of treatment. Given these effect estimates, with an alpha of 0.05, an 80% power, and a 20% attrition, we estimated a sample size of approximately 96 (48 per group) will be needed. This randomized controlled trial will use an ANOVA and t-test (alpha error level = 5%, two-sided) for independent samples.

This sample size will require tailored recruitment efforts, community partnerships, and culturally safe retention strategies throughout the trial. Given differential attrition rates for racialized communities, the research team will spend additional time at intake discussing barriers to participation, issues with attendance, and address any participant concerns. Additionally, the research team will offer flexible session meeting times (e.g., evenings and weekends), and telephone check-ins as needed. The research team shall also compensate participants for both their completed sessions and batteries of measures.

In terms of blinding, the trial research team will be unaware of the group allocation. This includes the principal investigator and project coordinator who are overseeing the trial implementation, research assistants who will support recruitment and data collection, and the statistician conducting the analysis. See Figure 1 for the participant flow diagram of the trial.

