### 2.12. Statistical Analysis

Descriptive statistics, including means, standard deviations, and frequencies, will be calculated for continuous primary and secondary outcomes. Differences in primary and secondary outcomes, including TSDS, RTS, change in symptoms, and therapeutic experiences, will be examined using a two-way mixed ANOVA with two or three within-subject levels of time (pre-test, post-test, and follow-up) and two between-subject levels of condition (HRTP and control). When there is evidence of sphericity violation, we will use the Greenhouse–Geisser correction (Greenhouse & Geisser, 1959). It is predicted that participants’ TSDS and RTS scores will decrease significantly over the course of the treatment. It is also predicted that TSDS and RTS scores at follow-up will be the same or lower than at the end of the treatment.

Both the short-term and long-term efficacy of the HRTP will be examined during the treatment (week 0, 4, 8), at the end of the treatment (week 12), and 4 months after the treatment (week 28). Assessment will take place at four time points for the treatment group (HRTP therapy; weeks 0, 4, 8, 12, and 28; see Table 1 for participants’ assessment schedule) and only two time points for the control TAU group (T0 and T4; see Table 1 for participants’ assessment schedule). Analysis will compare standard mean differences (SMDs) between the time points for the treatment group (weeks 0, 12, and 28) and the control group (weeks 0 and 12). Analyses will entail intent to treat (ITT) and include participants with pre-treatment and the last time point available as long as they attended at least one treatment session. We examine significant levels for the analysis as well as effect sizes. A significance level of *p* < 0.05 will be used for all tests.

For each outcome of interest, we will identify any significant Condition × Time interactions. When no interaction is found, significant main effects will be reported. Partial eta-squared (η2) was used to measure effect sizes for the ANOVAs. When significant interactions are found, post hoc tests of simple main effects will be used to examine the differences, *p* values will be included for all post hoc tests, and 95% confidence intervals (CIs) will be used for all *p* values less than 0.05. Additionally, we will conduct comparisons of baseline data for completers and non-completers. Subgroup analysis will be based on age, gender, and levels of racial stress and trauma.

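### The effect measures named in the analysis section are not the between-arm SMD the trial is sized on, and a non-significant result would carry no HRTP-versus-TAU estimate with a confidence interval

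*Protocol article*

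**What the plan says.** Section 2.2 states the sizing hypothesis as a contrast between arms at the end of treatment: "we hypothesized a standard mean difference of between 0.36 and 0.52, between the treatment and control group". It continues: "Given these effect estimates, with an alpha of 0.05, an 80% power, and a 20% attrition", and says that the trial "will use an ANOVA and t-test (alpha error level = 5%, two-sided) for independent samples".

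Section 2.12 names two effect measures. The first is: "Analysis will compare standard mean differences (SMDs) between the time points for the treatment group (weeks 0, 12, and 28) and the control group", where the control group's weeks are 0 and 12. No standardiser is given. The second is: "Partial eta-squared (η2) was used to measure effect sizes for the ANOVAs".

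The efficacy test in section 2.12 is the Condition × Time interaction of a mixed ANOVA. Simple main effects follow only if that interaction is significant; otherwise significant main effects are reported. Confidence intervals at the 95% level are tied to p values under 0.05. Means and SDs are planned as descriptive statistics for the continuous outcomes.

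**The concern.** The trial asks whether HRTP reduces symptoms more than TAU, and by an amount that matters clinically. That calls for a between-arm difference with a sign and an interval, on a scale that can be compared with 0.36 to 0.52. Neither measure named in section 2.12 is that quantity. A pre-post SMD describes change within one arm. Partial eta-squared describes a share of variance and has no direction.

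The gap matters most for a non-significant result. An interval around the between-arm difference would then show whether the hypothesised effect had been ruled out or merely not detected, and the plan's rule for intervals leaves it out in exactly that case. Readers would be left with two within-arm SMDs side by side, which invites a comparison that can mislead if each has its own denominator.

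**Working it through.** **1. The plan's own figures.** The SMD range 0.36 to 0.52, two-sided alpha 0.05, 80% power, 20% attrition and the total of 96 come from section 2.2. With n per arm = 2(1.960 + 0.842)²/SMD², the SMDs 0.52 and 0.36 give 59 and 122 per arm. Dividing by 0.8 and rounding up gives 74 and 153, or totals of 148 and 306. The stated 96 is not reproduced. That is a separate matter; 96 is used below only to set the number expected to be analysed: 96 × 0.80 = 76.8, about 77, or 38 per arm.

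**2. What kind of SMD each section means.** Section 2.2 contrasts the two groups. Section 2.12 contrasts time points and gives each arm its own list of weeks. Section 2.9 and Table 1 give TAU no week-28 assessment, so any SMD involving week 28 can only be within HRTP. Within-arm SMDs are therefore the natural reading, though not the only one.

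**3. Partial eta-squared against the planned SMD.** For two arms and two time points, with pre-post correlation r (not given, so assumed):

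- d_change = d / √(2(1 − r))
- F = (N/4) × d_change²
- partial eta-squared = F / (F + N − 2)

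For d = 0.52, r = 0.5, N = 77: d_change² = 0.2704, F = 19.25 × 0.2704 = 5.21, and 5.21/80.21 = 0.065.

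| Between-arm SMD | r = 0.3 | r = 0.5 | r = 0.7 |
|---|---|---|---|
| 0.36 | 0.023 | 0.032 | 0.053 |
| 0.52 | 0.047 | 0.065 | 0.104 |

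The large-sample form d_change²/(d_change² + 4) gives 0.046, 0.063 and 0.101 for 0.52. One true effect spans more than a two-fold range. The low end of the hypothesis at r = 0.7 (0.053) exceeds the high end at r = 0.3 (0.047), so the statistic does not even rank the two without r. When raw changes are equal, d = 0 and the population value is 0 at every r.

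**4. Within-arm SMDs with separate denominators.** SMD = raw change / SD. For the same 7.5-point drop: 7.5/15 = 0.50, 7.5/18 = 0.42, 7.5/20 = 0.38. The apparent gap is 0.08 to 0.13 (0.500 − 0.417 and 0.500 − 0.375) with no difference in change. The SDs and the drop are assumptions. With one common SD the gap is 0.

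If the true SDs are equal and each arm uses its own baseline SD, the gap centres on 0. Its chance SD is roughly δ/√(n − 1), where δ is the change in SD units. For δ = 0.5 that is 0.5/√47 = 0.073 and 0.5/√37 = 0.082; simulation with 48 and 38 per arm gave 0.076 and 0.087. For δ = 0.8, simulation gave 0.122 and 0.138, with a gap beyond 0.2 in 10% and 14% of trials.

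**5. How likely the case without an interval is.** Power of the interaction test with 38 per arm ≈ Φ(d_change × √19 − 1.96).

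| Between-arm SMD | r = 0.3 | r = 0.5 | r = 0.7 |
|---|---|---|---|
| 0.36 | 26% | 35% | 53% |
| 0.52 | 48% | 62% | 83% |

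A non-significant interaction is thus a realistic outcome even if the hypothesised effect is true. The fallback on main effects does not help. A main effect of time is not a treatment effect. A main effect of condition averages weeks 0 and 12, so with balanced baselines it carries (0 + d)/2, half of the week-12 difference.

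**The case against.** The strongest defence is that the inference is sound. The Condition × Time interaction tests the between-arm difference in raw change, and nothing in section 2.12 makes the comparison of within-arm SMDs a decision rule. That stands. A reader might infer that the efficacy test is compromised or that false positives rise; the document does not support this.

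A reader might also infer that equal raw change could show up as a treatment effect in partial eta-squared. It cannot: step 3 gives a population value of 0. For the SMDs the consequence needs arm-specific denominators, and none is named. With a common SD, the difference between the two SMDs is itself a between-arm SMD of change. Nor does the document show that TAU scores spread more widely. Section 2.7 lists several therapies in the TAU clinic, but that says nothing about outcome variance, and randomization makes baseline SDs equal in expectation. No systematic direction can be claimed.

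Two further objections hold in part. The exact standardiser may sit in a fuller document; but the article does state its effect measures and its rule for intervals, and those are what do not fit section 2.2. And if means and SDs are published by arm and visit, a reader could work out a week-12 SMD. That is a reconstruction, not a prespecified estimate. Finally, partial eta-squared is a conventional companion to an ANOVA, and asking for its removal would be a preference.

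**Conclusion.** The mismatch is real and worth correcting, as a defect of estimation and reporting rather than of testing. The trial is sized on a signed between-arm SMD of 0.36 to 0.52. The measures named in section 2.12 do not deliver it, and the rule for intervals withholds one when the interaction is not significant.

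That partial eta-squared is unsigned and needs the pre-post correlation to be converted holds without further assumption; the two-fold spread rests on assumed correlations of 0.3 to 0.7. The 0.08 to 0.13 gap between within-arm SMDs is conditional on arm-specific denominators and on assumed SDs of 15 against 18 or 20. It illustrates what the wording permits and does not forecast a bias.

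**What to change.** In section 2.12, for each primary outcome, define the reported effect as the HRTP-minus-TAU difference at week 12 in scale points, and the same difference divided by the pooled week-0 SD of both arms. Give each with a 95% confidence interval whatever the p value, and remove the condition on p for these estimates.

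Keep within-arm changes, including the HRTP change to week 28, as description, and state that within-arm SMDs are not compared across arms as evidence of a treatment effect. Partial eta-squared may stay as a supplement to the ANOVA.

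The cost is a few sentences and a minor analysis. Both arms are already assessed at weeks 0 and 12, so no new data are needed.

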Moreover, the research team will use targeted emails, social media posts, local bus ads, and word of mouth to advertise the study, instructing interested individuals to reach out to a study-specific email address. Once interest is confirmed, an email response will be sent with detailed information about the study and a consent form for consideration. The said study-specific email address will also present a direct contact with whom prospective participants may communicate should they have any questions or concerns about the study. Those interested in moving forward will be invited to partake in a 3 h virtual intake session (See Table 1 for the participants’ assessment schedule). During this intake, a trained research assistant will (i) describe important elements of the study, including the participant’s role and responsibilities; (ii) collect the necessary information from the participant to start a “file” (e.g., date of birth, gender, occupation, ethnoracial identity, contact information, emergency contact); (iii) and administer two semi-structured diagnostic interviews (i.e., the Mini International Neuropsychiatric Interview as well as the University of Connecticut Racial/Ethnic Stress & Trauma Survey). A 15 min break will be provided at the halfway point of the intake session. Using this intake information, the research team will continually and iteratively assess the demographic characteristics of the enrolled participants, gender and otherwise, to ensure sample heterogeneity and the generalizability of the findings (e.g., age, ethnicity, immigrant status, and socioeconomic status). Participant personal information and identifiers will be stored in a data management system to ensure participant privacy protection and data security. Data used for analysis will only include unique identification numbers assigned to each participant at intake. The data will be published in aggregate form and no participant identifier will be included.

Following intake, the participants will be randomly assigned to one of two groups: the HRTP (intervention) group or the control group (TAU). The randomization will be conducted using a computer-generated randomization sequence with stratification by age, gender, and the baseline level of racial stress (via the Racial Trauma Scale; Williams et al., 2022b).

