### 2.4. Participant Retention Strategies

The research team will use a range of equitable and inclusive strategies to ensure participant retention and mitigate attrition throughout the study. Once participants have completed the intake process and are fully onboarded, they will be assigned to a treatment group and a therapist. Through the sessions, the research team, including the therapists, will work with participants to sustain their participation and address barriers to their participation as they emerge. Participants will receive reminders based on their contact preferences, as well as notifications on our platform, for information about their sessions, questionnaires to complete, and any updates from the therapist and research team. Weekly sessions will be scheduled collaboratively with participants with flexibility incorporated into the available hours, and with the scheduling and rescheduling of sessions as needed. This flexibility will ensure therapists can identify and address any relevant barriers to a participant’s involvement. If a participant misses two sessions without further follow-ups with the research team, they will be invited to reconsider a better time to join the project. Further, participants will be paid for each session and packet of measures completed. For instance, within a pilot study of the HRTP trial, participants received $5 for each session as well as $30 for each battery of measures completed (e.g., intake and week 4).

The approach and strategies of this study are specific to racialized communities recognizing the historical and contemporary barriers to research access and participation. Specifically, we recognize participants will need explicit information and engagement as many might not have prior experience of participating in a clinical treatment study. Additional effort and time will be taken to answer participant questions, explain the process of their participation, and flexibility will be built into the design to support their continued involvement. These methodological considerations are essential to working with racialized communities experiencing racial trauma and the design and implementation are deliberate to centre the concerns of these communities to ensure their equitable and inclusive participation.

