### 2.9. Primary Outcomes

Three primary outcomes will be measured at five time points for the treatment group (weeks 0, 4, 8, 12, and 28) and twice for the TAU control group (weeks 0 and 12). See Table 1 for the participants’ assessment schedule. Of note, there will be a differential assessment schedule for TAU versus HRTP participants. That is, HRTP participants are assessed on three more occasions than those in the TAU group. Two of these additional assessment periods are included within the intervention arm’s active treatment phase (weeks 4 and 8) to better understand how each HRTP phase impacts healing/racial trauma symptom severity. Week 4 roughly translates to the participants transitioning to the Healing phase and week 8 the Empowerment phase. Further, those in the control arm have no need for a post-treatment follow-up as upon receiving TAU, they may be immediately enrolled within the treatment group to receive the HRTP.

The *Racial Trauma Scale* (RTS; Williams et al., 2022c) is a 30-item clinical measure which examines the severity of traumatic symptoms due to racism. More specifically, the RTS asks individuals to “think about all the times when you have heard about, seen, or experienced racial discrimination” and how much they have been bothered by resultant thoughts, behaviours, or symptoms on a 4-point scale (where 1 is “not at all” and 4 is “extremely”). Of note, within this study specifically, when completing the RTS, clients will be asked to rate symptoms as per their lived experience over the previous month/30 days. An RTS total score is calculated by summing all item ratings together. Moreover, subfactors of the RTS include “Lack of Safety”, “Negative Cognitions”, and “Difficulty Coping”. Higher RTS total and subfactor scores indicate greater symptom distress. In consideration of the RTS’s convergent validity, RTS responses were found to be highly correlated with several measures of trauma, including the *PTSD Checklist for the DSM-5* (PCL-5; r = 0.79) and the *General Ethnic Discrimination Scale* (r = 0.76). The RTS was developed for and tested with diverse ethnoracial populations. The RTS also has excellent reliability (α = 0.97; Williams et al., 2022c).

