## Figures and Tables

**Figure 1 behavsci-15-00856-f001:**
[figure not shown]
Participant flow diagram in HRTP Trial.

**Table 1 behavsci-15-00856-t001:** Participant assessment schedule.

Time	Session	Week	Measures	
			Intervention Group	Control/TAU Group
T1	Intake	0	MINI; UnRESTS; BDI-II; RTS; TSDS	
T2	4	4	BDI-II; RTS; TSDS; HAq-II; RMCS	nothing
T3	8	8	BDI-II; RTS; TSDS; HAq-II; RMCS	nothing
T4	12	12	BDI-II; RTS; TSDS; HAq-II; RMCS	BDI-II; RTS; TSDS; HAq-II; RMCS
T5	Follow Up	28	BDI-II; RTS; TSDS	participants will have withdrawn from the study or started the protocol

Note. BDI-II: Beck Depression Inventory-II; HAq-II: Helping Alliance Questionnaire-II; MINI: The Mini International Neuropsychiatric Interview; RMCS: Racial Microaggressions in Counselling Scale; RTS: Racial Trauma Scale; TSDS: Trauma Symptoms of Discrimination Scale; UnRESTS: University of Connecticut Racial/Ethnic Stress & Trauma Scale.

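### The analysis set labelled intent to treat drops randomised participants with no session, and its last-time-point rule can treat dropouts differently by arm because the visit schedules differ

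*Protocol article*

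**What the plan says.** Section 2.12 of the protocol article states "Analyses will entail intent to treat (ITT") and defines the set in the same sentence: it will "include participants with pre-treatment and the last time point available as long as they attended at least one treatment session".

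Four other places bear on how that sentence works.

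- **Timing of randomisation (section 2.3):** "Following intake, the participants will be randomly assigned to one of two groups". Sessions start only after that.
- **Schedules (section 2.9):** the primary outcomes are measured at "weeks 0, 4, 8, 12, and 28) and twice for the TAU control group (weeks 0 and 12"). The section adds that "HRTP participants are assessed on three more occasions than those in the TAU group". Table 1 agrees, and its TAU entry for week 28 reads "participants will have withdrawn from the study or started the protocol".
- **Comparison (section 2.12):** standardised mean differences are compared "between the time points for the treatment group (weeks 0, 12, and 28) and the control group (weeks 0 and 12").
- **Missed sessions (section 2.4):** of people who miss two sessions without further contact with the team, the article says "they will be invited to reconsider a better time to join the project".

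The only other provision about incomplete participants is a baseline comparison of completers with non-completers (section 2.12).

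**The concern.** Two things are wrong with the sentence as it stands.

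First, the label and the rule contradict each other. Attending a session is a post-randomisation event. Excluding those who attend none gives up the protection of randomisation for that group, while readers are told the analysis is ITT.

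Second, the last available time point is not the same thing in the two arms. An HRTP participant who stops can have a week 4 or week 8 score, and an HRTP completer can have a week 28 score. A TAU participant who misses week 12 has baseline and nothing else. The text does not say whether that person is counted as unchanged or left out. The same dropout can therefore be handled differently by arm, and an undefined choice at analysis can move the primary result.

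**Working it through.** The article gives no figure for this effect, so there is none to reproduce. The check asks what the rule does when the two treatments work equally well.

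**Inputs from the article.** 48 per group and 20% attrition (section 2.2), so about 48 × 0.20 = 9.6, or 10 people per arm, without week 12. Visits are as in section 2.9 and Table 1. Pilot dropout was 4 of 14 = 28.6%, HRTP only (section 2.11).

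**Assumptions, not in the article.** Both arms improve by the same amount D = 0.3, 0.5 or 0.8 SD, linearly to week 12. Dropout is unrelated to outcome. HRTP dropouts are last seen either equally at weeks 0, 4 and 8, or all at week 8. Write p for the dropout proportion, with subscripts H (HRTP) and T (TAU).

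**Reading A: carry forward, TAU dropouts counted as unchanged.** With HRTP dropouts spread over weeks 0, 4 and 8, their mean carried change is D × (0 + 1/3 + 2/3)/3 = D/3. TAU dropouts contribute 0. With equal p the spurious difference favouring HRTP is pD/3. If all HRTP dropouts are last seen at week 8, it is 2pD/3.

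**Reading B: carry forward, anyone with baseline only excluded.** The TAU mean is D. In HRTP a proportion p/3 is excluded and 2p/3 carry D/2 on average, so the mean is D(1 − 2p/3)/(1 − p/3). The difference against HRTP is D(p/3)/(1 − p/3). At p = 0.20 this is 0.0667/0.9333 × D = 0.071D.

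| D (SD) | A, spread: 0.2D/3 | A, all week 8: 0.4D/3 | B, spread: 0.071D |
|---|---|---|---|
| 0.3 | 0.020 for HRTP | 0.040 for HRTP | 0.021 against |
| 0.5 | 0.033 for HRTP | 0.067 for HRTP | 0.036 against |
| 0.8 | 0.053 for HRTP | 0.107 for HRTP | 0.057 against |

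Against the hypothesised effect of 0.36 to 0.52, the extremes for reading A are 0.020/0.52 = 4% and 0.107/0.36 = 30%. The second pairs the largest bias with the smallest effect.

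**Unequal dropout, reading A, spread timing.** The difference favouring HRTP is D(p_T − 2p_H/3).

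- p_H = 0.286, p_T = 0.20: (0.200 − 0.191)D = 0.009D, at most 0.007 SD.
- p_H = 0.20, p_T = 0.286: (0.286 − 0.133)D = 0.153D, or 0.05 to 0.12 SD.

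**Simulation** (48 per arm, visit correlation 0.6 assumed, spread timing, 4,000 runs, no true difference). At 20% dropout in both arms, reading A gave 0.02 to 0.05 SD for HRTP, with type I error 4.4% to 6.2%. Reading B gave 0.02 to 0.06 SD against. With 28.6% dropout in TAU and 20% in HRTP, reading A gave type I error of 6.3% to 11.3%. Comparing both arms on observed week-12 scores, with nothing carried, gave differences of −0.007 to +0.005 SD and type I error of 4.2% to 5.5%.

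**Reading C: both a pre-treatment and a final score required.** Nothing is carried and the schedules no longer matter. About 48 × 0.80 = 38 per arm remain. This is a completer set, valid only if dropout is unrelated to outcome, and it is not ITT.

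**Exclusion for attending no session.** The article gives no rate, so this part is not quantified.

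**The case against.** The strongest objection is that carry-forward is only one reading. The preceding sentence of section 2.12 names weeks 0, 12 and 28 for HRTP and 0 and 12 for TAU, with no week 4 or 8 scores, which suits reading C. On that reading the carried-score mechanism and its magnitudes fall away. This stands as a limit on the second part of the point, but it does not rescue the label: a completer set is further from ITT than the one-session rule alone.

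It is also fair to say that the size rests on assumed improvement and dropout timing. HRTP participants who leave before week 4 have only baseline, just like a TAU dropout. At equal 20% dropout with spread timing, the simulated type I error is close to nominal. The pilot rate is 4 of 14 (exact 95% interval about 8% to 58%) and comes from HRTP alone, so applying it to TAU is only an illustration.

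A reader might infer that TAU participants will more often attend no session because they did not get the therapy they came for. The article does not show this. TAU participants are to receive 12 sessions, participants are paid per session, and HRTP is offered to them later, all of which encourage attendance. A reader might also infer from section 2.4 that people who miss two sessions are removed from the trial. The text only invites them to reconsider timing, after no further contact, and does not say their assessments stop.

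Finally, an unseen analysis plan may choose the missing-data method. That does not excuse a rule which the article itself states and which is wrong as written.

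**Conclusion.** The point holds in two parts of different strength. That the stated set is not ITT follows from the text alone, with no assumption. That the last-time-point rule can treat dropouts differently by arm holds if it means carry-forward. The spurious difference is then about 0.02 to 0.11 SD at 20% dropout in both arms, for an assumed linear improvement of 0.3 to 0.8 SD. The direction depends on how baseline-only TAU participants are handled, and the effect is near zero if HRTP dropout is 28.6% and TAU dropout 20%.

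It would be tempting to conclude that the primary comparison is biased in favour of HRTP. The article does not support that: it fixes neither the reading, the sign nor the dropout pattern. The supportable statement is that the rule is mislabelled and ambiguous, and that one natural reading can bias the result either way by a modest amount.

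**What to change.** Replace the sentence in section 2.12 with a statement that:

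1. the primary analysis includes all randomised participants in their assigned arm, whatever number of sessions they attended;
2. the arms are compared at week 12, the only post-baseline visit they share, using a likelihood-based repeated-measures model or multiple imputation, with no earlier score carried forward;
3. the week-12 questionnaires are sought from everyone, including those who stop sessions;
4. the set with at least one session is used only as a sensitivity analysis.

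If the repeated-measures model is chosen, baseline should enter as one of the modelled outcomes. With baseline only as a covariate, a TAU participant without week 12 would drop out of the model again.

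The cost is a change of wording and the effort of chasing week-12 questionnaires, from about 10 people per arm at the planned attrition. The downside is a missing-at-random assumption. In TAU it rests on baseline alone, whereas HRTP also has weeks 4 and 8, so it should be checked by sensitivity analysis. The collection step must be settled before participants reach week 12, because scores not collected then cannot be recovered.

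### Three outcomes are declared primary but only two are powered and predicted, and each is tested at an unadjusted 0.05 with no order of testing or success rule

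*Protocol article*

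**What the plan says.** The protocol article describes its primary outcomes in several places.

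- Sections 2.8 and 2.9 count three primary measures and describe them as RTS, BDI-II and TSDS: "Three primary outcomes will be measured at five time points for the treatment group". The control arm has them at weeks 0 and 12 only.
- Section 2.1 works with domains: "racial trauma, depression (primary outcomes), and functioning (secondary outcomes".
- Section 2.2 bases the power analysis on the means, standard deviations and "clinical cut-off for the primary outcomes (RTS, TSDS". BDI-II does not appear in that section.
- Section 2.12 names TSDS and RTS in an open list of outcomes, predicts the course of those two scores only, and looks for a Condition × Time interaction on each outcome separately. It says that a significance level of "0.05 will be used for all tests".

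The article states no division of alpha, no order of testing, no lead outcome and no requirement that all primaries succeed.

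**The concern.** There are two linked problems.

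The first is that the status of BDI-II is unsettled. Sections 2.8 and 2.9 make it one of three primaries, while section 2.2 treats the primary set as RTS and TSDS. A reader cannot tell whether a BDI-II result, positive or null, bears on the primary conclusion, or what effect on it the trial was designed to detect.

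The second is that the one rule the article fixes for significance is the same unadjusted level for every test. With two or three primaries and no rule for combining them, the choice of what counts as success stays open until the results are known. A reading under which one positive scale is enough would carry a false-positive rate above the 5% that the sample-size section assumes.

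**Working it through.** **1. The primary set, section by section**

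| Section | Primary set |
|---|---|
| 2.1 | racial trauma and depression (domains) |
| 2.2 | RTS, TSDS |
| 2.8 and 2.9 | RTS, BDI-II, TSDS |
| 2.12 | no set listed; predictions for TSDS and RTS only |

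Section 2.1 fits sections 2.8 and 2.9, since RTS and TSDS cover racial trauma and BDI-II covers depression. The firm conflict is between sections 2.8/2.9 and section 2.2. The predictions in section 2.12 follow the shorter set.

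**2. The plan's own figure**

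Inputs from section 2.2: "with an alpha of 0.05, an 80% power, and a 20% attrition", two-sided, and "we hypothesized a standard mean difference of between 0.36 and 0.52". For two independent means, n per arm = 2(1.960 + 0.842)² / SMD².

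- SMD 0.36: 122 per arm, 244 in total; after 20% attrition, 122/0.8 rounds up to 153 per arm, 306 in total.
- SMD 0.52: 59 per arm, 118 in total; after attrition, 59/0.8 rounds up to 74 per arm, 148 in total.

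The stated 96 is not reproduced. A baseline-adjusted analysis with an assumed pre-post correlation of 0.6 and SMD 0.52 would give 76 before and 96 after attrition, but the article states no such correlation. The sample size is a separate matter. It is used here only because it determines what an alpha split would cost.

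**3. Chance of at least one false positive, if any one primary suffices**

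Under independence: three tests, 1 − 0.95³ = 0.143; two tests (RTS and TSDS), 1 − 0.95² = 0.0975.

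With correlated tests, by simulation of equicorrelated normal statistics (1,000,000 draws, two-sided, critical value 1.96):

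| Assumed correlation | Any of three | Any of two |
|---|---|---|
| 0.5 | 12.5% | 9.05% |
| 0.7 | 10.9% | 8.4% |
| 0.8 | 9.8% | 7.8% |
| 0.9 | 8.3% | 7.0% |

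The article gives no correlations among the three scales, so these are assumptions. It does report correlations with the PCL-5 of 0.79 for RTS and 0.69 for TSDS (section 2.9), which makes independence of those two implausible.

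**4. Fixed sequence**

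Each test is at 0.05 and is carried out only if all earlier ones succeeded. A false claim requires rejecting the first true null hypothesis in the order, which has probability at most 0.05. The family-wise rate is therefore at most 5% whatever the correlations, and the first outcome keeps the full 0.05.

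**5. Holm across three co-primaries**

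The first step is at 0.05/3 = 0.0167, with critical value 2.394. Power = Φ(SMD × √(n/2) − critical value).

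- 48 per arm, √24 = 4.899: SMD 0.36 gives Φ(1.764 − 2.394) = 26%; SMD 0.52 gives Φ(2.547 − 2.394) = 56%.
- 38 per arm (48 × 0.8 = 38.4): 21% and 45%.
- At 0.05 instead, the values are 42% and 72% with 48 per arm, and 35% and 62% with 38.

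For 80% power at 0.0167 on a single outcome, the totals are 324 (SMD 0.36) or 156 (SMD 0.52) before attrition, and 406 or 196 after.

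**The case against.** The strongest reply is that the article never says that one positive scale makes the trial a success. A reader might infer an any-of-three rule from the blanket 0.05, but section 2.12 sets a threshold for each test and promises effect sizes and p values outcome by outcome. It defines no trial-level criterion. If all three primaries had to succeed, the error rate would not be inflated. This stands, and the inflation must be stated as conditional. A success rule is also something an article may leave to a full protocol or analysis plan, neither of which is shown. That does not dispose of the point, because the article does more than stay silent: it fixes 0.05 for all tests, and an adjustment elsewhere would contradict it.

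Two further inferences are tempting and not supported. One is that section 2.1 also contradicts the three-measure set; it names domains that all three measures fit. The other is that BDI-II is left out of the analysis. The list in section 2.12 is open-ended and each outcome of interest is tested, so BDI-II can be covered, and the abstract names reduced depression symptoms as an aim. What remains is that BDI-II has no assumed effect, no power basis and no prediction in the analysis section.

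It is also fair to say that RTS is not the only possible lead. TSDS is in the power statement too and bears on racial trauma. RTS has the further advantage that it is the stratification measure (section 2.3).

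**Conclusion.** The concern holds in a limited form. The primary set is inconsistent between sections 2.8/2.9 and 2.2, with the predictions in section 2.12 following the shorter set. This holds whatever view is taken of multiplicity. Separately, the article fixes a rule for the primaries that does not control the family-wise error.

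If any one of three primaries suffices, the error is about 8% to 12.5% for assumed correlations of 0.9 to 0.5, against a nominal 5%. The 14.3% under independence is an upper limit rather than the expected rate, because RTS and TSDS measure related constructs. If only RTS and TSDS are primary, it is about 8.4% at an assumed correlation of 0.7. The documents do not support saying that the trial has adopted an any-of-three rule, or that its false-positive rate is 14.3%.

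**What to change.** Make sections 2.2, 2.8, 2.9 and 2.12 name the same primary set, and replace the blanket 0.05 rule for the primaries. Suggested text for section 2.12:

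*The primary comparisons are between arms at week 12, two-sided at 0.05, in this order: RTS total, TSDS, BDI-II. Each is tested for a confirmatory claim only if all those before it are significant. Other results are reported with estimates and confidence intervals and carry no confirmatory claim.*

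Week 12 is the only post-baseline visit that Table 1 schedules for both arms. RTS comes first because it fits objective (a) in section 1.4, is in the power statement and is the stratification measure. HAq-II and RMCS remain secondary outcomes and the 28-week maintenance question remains an objective; they keep their declared status and are reported without a confirmatory claim outside the sequence. Section 2.2 should state the effect assumed for BDI-II, or say that the trial is not powered for it.

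The change needs no extra participants or visits. The cost is that a confirmatory claim on TSDS or BDI-II becomes conditional on RTS, which matters for depression because section 2.1 calls it primary.

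If the sponsor prefers three co-primaries of equal standing, Holm controls the error rate. The plan should then state the cost: about 26% to 56% power at the first-step level with 48 per arm for SMD 0.36 to 0.52, before attrition.
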